#### Interim Analyses

We neither planned nor performed an interim analysis.

#### Methods for Additional Analyses (eg, Subgroup Analyses)

Age and severity of critical illness as predictors of poor outcomes and practice might differ between centers, so randomization was stratified by center and statistical analysis is adjusted for these factors to minimize discrepancies between therapeutic groups.

#### Methods in Analysis to Handle Protocol Nonadherence and Any Statistical Methods to Handle Missing Data

Intent-to-treat statistical analysis will be performed after all patients have completed the 1-year follow-up. Accordingly, all patients will be analyzed in the arm they were allocated to, regardless of protocol deviations. In addition, missing outcome data will be imputed. Prior to any data analysis, a detailed statistical analysis plan will be drawn up by the study statistician. There will be a comprehensive report of the statistical analysis, following the CONSORT statement recommendations. Any change in the analysis plan will be justified in this final report.

While no missing data are expected, the maximum bias method will be used for analysis of the primary outcome, replacing missing data by a success in the control arm and by a failure in the intervention arm. For secondary outcomes, missing data will be handled by multiple imputations by chained equations. A sensitivity analysis of complete cases only will be performed.

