### Sample Size

At the time of the study design, other studies indicated that 10% of patients discharged from ICU died within the first year and 40% had a moderate to severe impairment on at least one dimension of the EQ5D [32,41].

Therefore, we estimated that at least 50% had a very poor outcome, combining death and severe to extreme impairment of at least one EQ5D dimension. [23]. The study was then powered to detect a decrease from 50% to 37% of patients with very unfavorable outcome with a power of 80% and a 2-sided 5% alpha risk, assuming this rate would be 50% in the control arm. Accordingly, the sample size was 249 patients per group. We anticipated that 20% of the patients would be lost to follow-up, so the sample size was increased to 300 per arm. The study therefore initially planned to enroll a maximal sample size of 600 patients. However, as the rate of loss to follow-up has, indeed, proved to be 10%, we decided to decrease the sample size to 520 patients. Finally, 546 patients were included. Interestingly, recent studies on comparable populations of critically ill patients showed that there was a 1-year mortality rate of between 10% and 28% [2,3,5,8,20] and that about 60% of patients had a moderate to severe impairment on at least one dimension of the EQ5D [3,10,29]. These findings suggest that our original estimation is still appropriate.

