### Statistical Methods

#### Statistical Methods for Primary and Secondary Outcomes

The 1-year survival rate without major deterioration in QoL (main endpoint, defined as reporting of death or a severe to extreme problem” level in 1 of the 5 dimensions studied) will be compared between both arms using a piecewise exponential model considering any censorship and the repeated nature of observations, prohibiting the use of conventional methods of analysis of censored data. This analysis will be adjusted for age and severity of critical illness (according to SOFA grading), and the center will be considered as a random effect. In addition, 2 analyses will be performed, according to age category (with cut-off at 65 years) and severity of critical illness (with a cut-off at the median value).

Binary outcomes will be analyzed using logistic regression. Absolute risk reductions will be obtained using a binomial model with identity link [49]. For time-to-event outcomes, Kaplan-Meier survival curves or cumulative incidence curves will be estimated, and the intervention effect will be analyzed using the Cox proportional hazards regression. Mixed linear regression will be used for continuous outcomes, possibly after variance-stabilizing transformation. All tests will be 2-sided at a .05 significance level.

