## Results

The study was funded by the Ministry of Health in June 2010. It was approved by the Ethics Committee on July 8, 2011. The first and last patient were randomized on December 20, 2012, and September 1, 2017, respectively. A total of 546 patients were enrolled across 11 ICUs. At present, data management is ongoing, and all parties involved in the trial remain blinded.

The first patient was recruited on December 20, 2012, and the last patient on September 1, 2017. The study was never suspended. The assessor of the primary endpoint and study statistician remained blinded to study intervention throughout the trial. Data management is ongoing. Release of the results is planned for end of 2022.

There were 10 amendments to study protocol (Multimedia Appendix 1). All amendments were approved by investigators, study statistician, AP-HP, CPP, and ANSM.

The DRRC organized data monitoring and quality audits. Baseline characteristics, eligibility criteria, primary outcome, secondary outcomes, and serious adverse events reported in the eCRF were systematically checked against original charts for all research participants. In addition, for one-third of the study population, all data reported in the eCRF were validated against a patient’s original chart. Serious adverse events and major protocol violations were reported to the DRRC, ANSM, and CPP. The study coordinator had quarterly face-to-face meetings with the DRRC and AP-HP to monitor trial conduct according to the highest standard for protection of research participants. All randomized patients completed follow-up for the primary outcome.

Monitoring of the data has been completed. Freezing of the database and statistical analysis are planned within the next 6 months.

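### Maximum-bias replacement governs the primary outcome; if the 10% loss used to resize the trial applies to that outcome, the 13-point design effect shrinks to 1.7 points and power to about 6%

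*Protocol article*

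**What the plan says.** The section on protocol nonadherence and missing data sets the rule: "While no missing data are expected, the maximum bias method will be used for analysis of the primary outcome", which it defines as "replacing missing data by a success in the control arm and by a failure in the intervention arm". Multiple imputation by chained equations is named for secondary outcomes only. A complete-case analysis is listed as a sensitivity analysis.

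Three statements bear on how much primary data is missing:

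- The same section expects none ("While no missing data are expected, the maximum bias method will be used for analysis of the primary outcome").
- Results reports: "All randomized patients completed follow-up for the primary outcome".
- Sample Size justifies reducing the target from 600 to 520 patients "as the rate of loss to follow-up has, indeed, proved to be 10" per cent.

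The primary analysis is a piecewise exponential model "considering any censorship and the repeated nature of observations" (Statistical Methods for Primary and Secondary Outcomes). A failure is death or a severe to extreme problem on an EQ5D dimension. On the design, Sample Size says: "The study was then powered to detect a decrease from 50% to 37% of patients with very unfavorable outcome". It sets power at 80% and alpha at 5%, two-sided, and gives the result as "the sample size was 249 patients per group".

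**The concern.** Maximum-bias replacement is a stress test. As the main handling, it builds a known bias into the estimate and its interval, and the bias grows with the amount of missing data whatever the treatment does.

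The sample size was not calculated for that analysis. It allows for loss by adding patients, as if lost patients simply leave the comparison. The missing-data rule keeps them in the denominator and scores them in opposite directions by arm. The stated 80% power therefore belongs to a different analysis once any appreciable share of the primary outcome is missing.

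The text also leaves open what happens to a patient lost before 12 months. The primary model is said to allow for censoring, while the missing-data section fills in a success or a failure. For one and the same patient, only one of these can be done.

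At stake are the chance of detecting the design effect and, if the intervention does nothing, the risk of reporting it as harmful.

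**Working it through.** **Inputs.** From Sample Size: failure rates 50% (control) and 37% (intervention), two-sided 5% alpha, 249 per group, 10% loss, revised target 520 (260 per arm), enrolled 546 (273 per arm if equal). The missing-data section supplies the replacement rule.

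**Assumptions not in the documents.** A fraction m is missing in each arm, equally and unrelated to outcome. A pooled two-proportion z-test stands in for the piecewise exponential model; two proportions are also what the sample size is stated in.

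**The plan's own figure.** With mean rate 0.435, n = [1.960 × √(2 × 0.435 × 0.565) + 0.842 × √(0.50 × 0.50 + 0.37 × 0.63)]² / 0.13², which rounds up to 228 per group. With continuity correction it is 243, within 3% of the stated 249. So 249 is reproduced closely enough. The inflation 249 × 1.2 = 299 matches the original 300 per arm.

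**Rates after replacement.**

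- Control: (1 − m) × 0.50
- Intervention: (1 − m) × 0.37 + m
- Difference: 0.13 − 1.13m, which is zero at m = 0.13/1.13 = 11.5%

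**Power for benefit.** Φ[(d − 1.960 × s0)/s1], where d is the difference, s0 the pooled standard error and s1 the unpooled one, with all randomised patients in the denominator. At m = 10% and 273 per arm, d = 0.450 − 0.433 = 0.017 and s0 and s1 are both 0.0425, so power is Φ(−1.56) = 5.9%.

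| Missing per arm | Control | Intervention | Difference (points) | Power, 260/arm | Power, 273/arm |
|---|---|---|---|---|---|
| 0% | 50.0% | 37.0% | 13.0 | 85% | 87% |
| 1% | 49.5% | 37.6% | 11.9 | 78% | 80% |
| 2% | 49.0% | 38.3% | 10.7 | 70% | 72% |
| 5% | 47.5% | 40.2% | 7.4 | 39% | 41% |
| 10% | 45.0% | 43.3% | 1.7 | 6% | 6% |

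At 10% missing, power stays between 5.7% and 6.2% for 249 to 300 per arm. Simulation with 200,000 replicates gives 5.6% at 260 and 6.2% at 273 per arm.

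**Comparison with complete cases.** At 10% loss, 234 of 260 per arm gives 81% power, and 246 of 273 gives 83%.

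**No true effect (50% in both arms), 273 per arm.** The analysed rates are (1 − m) × 0.50 and (1 − m) × 0.50 + m, so the difference is m against the intervention. The chance of a significant result against it is 7% at m = 2% (49% vs 51%), 21% at m = 5% (47.5% vs 52.5%) and 65% at m = 10% (45% vs 55%). The nominal figure in that direction is 2.5%.

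**If deaths are all known.** Assume 10% die in each arm and 10% of survivors are missing. Control is 0.10 + 0.9 × 0.40 = 46.0%, and intervention is 0.10 + 0.9 × 0.27 + 0.09 = 43.3%. The difference is 2.7 points and power is about 9% at 260 or 273 per arm.

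**The case against.** The strongest reply is that no primary data are missing. The two statements specific to the primary outcome both say so, and the one in Results reports follow-up already completed. The EQ5D was taken by telephone, separately from the 12-month visit, and death counts as an outcome, so loss from visits could be 10% while primary data are complete. The 10% may also be a mid-trial figure, since it was used to change the target. If so, the rule replaces nothing and power at 273 per arm is about 87%. This stands as a condition on the whole point. It does not remove it: Sample Size draws no distinction between visits and telephone contact, and applies the 10% to a calculation built on the primary endpoint. For the same reason a reader might infer that the three statements are incompatible. The documents do not show that; they show an apparent conflict that needs explaining.

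Second, the rule protects against a false claim of benefit, a complete-case sensitivity analysis is planned, and a detailed statistical analysis plan is promised. The protection is real, but a sensitivity analysis can give it without biasing the main estimate. The article fixes the primary handling itself, so this is not a detail it leaves open.

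Third, the reference to censoring is conditional, and a censoring-based model is a legitimate way to handle lost patients. That stands. There is no need to strike the reference; the two sections need only agree.

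**Conclusion.** The concern holds conditionally. Replacing missing primary outcomes in opposite directions by arm is a poor main analysis unless missingness is close to nil, and the article's own statements leave open whether it is nil or about 10%. At 10%, 11.3 of the 13 points are lost and power at 273 per arm drops from about 87% to about 6%. Even 2% missing brings it to about 72%, and 5% to about 41%. These figures rest on equal missingness unrelated to outcome and on the two-proportion approximation.

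Two stronger readings are tempting but not supported. The effect is not erased at 10%: 1.7 points remain, and full cancellation needs 11.5%. Nor is a useless intervention generally likely to be declared harmful: that chance is about 65% at 10% missing, but 21% at 5% and 7% at 2%. The fall in power should also be measured from 87%, the figure for the same 273 per arm, and not from the nominal 80%.

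**What to change.** Before database freeze:

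1. State how many primary outcomes are missing in each arm, and reconcile Sample Size, the missing-data section and Results. If the 10% refers to visits or to an interim count, say so.
2. Make multiple imputation, already named for secondary outcomes, the primary handling for patients not known to be dead, with known deaths counted as failures.
3. Keep maximum-bias replacement as a sensitivity analysis, optionally with a tipping-point analysis beside it.
4. Make the primary-model section and the missing-data section agree on whether a patient lost before 12 months is censored or imputed.

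The cost is a wording change to the protocol and analysis plan while the statistician is still blinded. If nothing is missing, the result is unchanged. The one real downside is that the headline result would no longer carry a worst-case guarantee against a false claim of benefit; the sensitivity analysis would still report it.

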#### Plans to Give Access to the Full Protocol, Participant-Level Data, and Statistical Code

Those with direct access in accordance with the laws and regulations in force, in particular articles L.1121-3 and R.5121-13 of the Public Health Code (eg, investigators, those responsible for quality control, monitors, CRAs, auditors, and others involved in collaborating on trials), will take all necessary precautions to ensure the confidentiality of information relating to the tested drugs, the trial, and the trial participants, especially with regard to their identity and the results obtained. The data thus collected during quality controls or audits are then made anonymous.

### Oversight and Monitoring

#### Composition of the Coordinating Center and Trial Steering Committee

The steering committee is composed of DF and TS who initiated the project, the methodologist and the sponsor’s representatives (DRCI and CRU APHP) appointed for this research. The steering committee aimed at deciding during the trial the procedures to be followed, taking note of the recommendations of the independent supervisory committee. It defined the general organization and conduct of the research, and coordinated the information. It also decided the appropriate methodology to conduct for unforeseen circumstances. During the trial period it will determine and monitor the progress of the research, particularly in terms of tolerance and adverse events.

#### Composition of the Data Monitoring Committee, Its Role, and Reporting Structure

There was no Data Safety Monitoring Board (DSMB) as the intervention was considered safe for the patient.

### Adverse Event Reporting and Harms

Any adverse event occurring during the trial period was reported by participating centers via a centralized phone and email system. Serious adverse events and major protocol violations were reported to the DRCI and CPP.

### Plans for Communicating Important Protocol Amendments to Relevant Parties (eg, Trial Participants, Ethical Committees)

All substantial modifications to the protocol by the coordinating investigator were sent to the sponsor for approval. After approval was given, the sponsor obtained approval from the CPP (Research Ethics Committee) and authorization from the Agence Nationale de Sécurité du Médicament (ANSM) within the scope of their respective authorities before the amendment was implemented.

The information note and the consent form had been revised, particularly in case of a substantial amendment to the study.

### Dissemination Plans

Neither the study sponsor nor the study funder had any role in designing the trial, managing, analyzing, or interpreting the data, writing the report, or in the decision to submit the report for publication.

### Patient and Public Involvement

No patient involved.

### Availability of Data and Materials

In accordance with Good Clinical Practice: (1) the sponsor is responsible for ensuring all parties involved in the study agree to guarantee direct access to all locations where the study will be carried out, the source data, the source documents, and the reports, for the purposes of the sponsor’s quality control and audit procedures or inspections by the competent authority; (2) the investigators allow individuals in charge of monitoring and quality control to have access to the documents and personal data strictly necessary for these tasks, in accordance with the statutory and regulatory provisions in force (Articles L.1121-3 and R.5121-13 of the French Public Health Code).

The AP-HP had full access to patients’ charts and checked all data recorded in the eCRF against original charts. All information required by the protocol had to be provided in the electronic logbook and an explanation given by the investigator for any missing data.

### Ethics Approval and Consent to Participate

Methodological aspects were independently approved by the national jury of the Clinical Research Hospital Program in 2010, and the Ministry of Health confirmed funding under contract number AOM10072. The protocol and qualification of all investigators were approved by the CPP of Saint-Germain-en-Laye, France, on July 08, 2011. The CPP allowed for waiver of consent and deferred consent (number 11052). The trial was registered at Clinicaltrials.gov identifier NCT01796509 (registered on February 21, 2013).

Written informed consent of the patient had to be obtained by the investigator of the participating center. In case of impaired consciousness, the investigator sought for written consent from the next of kin. If the latter was not present, the patient could be included as deferred consent, as has been approved by the Ethics Committee, according to French law (Art L1122-1-2 du Code de la Santé Publique). As soon as the patient’s status allowed, written informed consent for the continuation of the research and analyses of the data was obtained. A copy of the consent form was given to every patient. The original copy must be retained in the investigator’s archive for a minimum of 15 years. A third copy is archived by the sponsor. Patients or the public were not involved in the design, or conduct, or reporting, or dissemination plans of our research.

## Results

The study was funded by the Ministry of Health in June 2010. It was approved by the Ethics Committee on July 8, 2011. The first and last patient were randomized on December 20, 2012, and September 1, 2017, respectively. A total of 546 patients were enrolled across 11 ICUs. At present, data management is ongoing, and all parties involved in the trial remain blinded.

The first patient was recruited on December 20, 2012, and the last patient on September 1, 2017. The study was never suspended. The assessor of the primary endpoint and study statistician remained blinded to study intervention throughout the trial. Data management is ongoing. Release of the results is planned for end of 2022.

There were 10 amendments to study protocol (Multimedia Appendix 1). All amendments were approved by investigators, study statistician, AP-HP, CPP, and ANSM.

The DRRC organized data monitoring and quality audits. Baseline characteristics, eligibility criteria, primary outcome, secondary outcomes, and serious adverse events reported in the eCRF were systematically checked against original charts for all research participants. In addition, for one-third of the study population, all data reported in the eCRF were validated against a patient’s original chart. Serious adverse events and major protocol violations were reported to the DRRC, ANSM, and CPP. The study coordinator had quarterly face-to-face meetings with the DRRC and AP-HP to monitor trial conduct according to the highest standard for protection of research participants. All randomized patients completed follow-up for the primary outcome.

Monitoring of the data has been completed. Freezing of the database and statistical analysis are planned within the next 6 months.

## Discussion

### Overview

PICS is a major public health issue, affecting more than half of critically ill patients 1 year after their discharge from an ICU [8]. It has a huge impact on QoL, affecting a patient’s personal, social, and professional life. In their Cochrane review, Schofield-Robinson et al [50] concluded that there was “insufficient evidence, from a limited number of studies, to determine whether ICU follow-up services are effective in identifying and addressing the unmet health needs of ICU survivors” and called for future studies that are “designed with robust methods (for example, randomized studies are preferable) and consider only one variable (the follow-up service) compared to standard care.” Our trial is in line with these recommendations as it is a multicenter parallel group RCT that was designed to determine whether a medical, psychological, and social follow-up improves QoL of the critically ill patient at 1 year after ICU discharge. This hypothesis was based on the fact that PICS is characterized by interdependent elements, which would be better targeted using a multidisciplinary approach. The SUIVI-REA trial is still original and relevant. Because the use of MV at a minimum of 3 days is an inclusion criterion enabling the selection of patients with severe critical illness, the results will be obtained from a representative population at risk of developing PICS. Its results could be then compared with those of ongoing trials assessing the benefit of telehealth [51], combined physical and cognitive training [52], or multidisciplinary personalized follow-up [53].

As cognitive impairment was not comprehensively assessed, it could be argued that it was not therefore managed. In 2010, when the study was designed, post-ICU cognitive dysfunctions were not identified as a major component of PICS. Moreover, we considered that compliance would have been reduced, as a cognitive assessment would have increased the length of the consultation period and the number of questionnaires patients had to complete. In our RCT, cognitive impairment was assessed using the MMS examination, which has been validated for detecting dementia and used in cohort studies of critically ill patients [20].

The program might be thought to be an assessment of physical, psychological, and social domains rather than one of multidisciplinary care. However, we felt that the multidisciplinary teams should not replace the physicians who routinely care for a patient but rather that they should contribute to patient care, notably by detecting ICU-related complications and suggesting specific management to the patient’s own doctor. Multidisciplinary teams were highly recommended to respect these deontological principles. For this reason, a concluding letter was systematically sent to the general practitioner, recapitulating the observations and propositions made by the multidisciplinary team. The impact of our intervention would therefore depend on the commitment of the multidisciplinary teams to participate in the patient’s overall care. Should our intervention not have added value to routine care, our hypothesis is that its main benefit would be the expertise of the multidisciplinary team to assess and treat ICU-related complications. In addition, the social assessment would help to personalize a patient’s care.

